### Secondary endpoint

1.3

The first secondary outcome to evaluate is the sensitivity/specificity of the pH test compared to the current Gold Standard (chest X-ray), also in consideration of clinical variables such as: food intake (time calculated in minutes from the last food intake, guaranteeing a minimum time to perform the test of at least 1 h) and taking drugs that affect gastric pH (proton pump inhibitors and antacids). Secondly, to evaluate the tolerance of the different NGT models used through pain monitoring (evaluated through the NRS scale at 24-48-72 h after placement and where an NRS score greater than ≥3 will be considered as a threshold value to identify poor tolerance). Thirdly, to evaluate the starting time of nutritional therapy from the request for placement of the NGT by the attending physician (calculated in minutes). Lastly, to evaluate possible complications associated with the positioning of the NGT and arising during the hospitalization period, such as: 1) mispositioning of the NGT (assessed with Chest X-ray); 2) tracheobronchial aspiration; 3) aspiration pneumonia 4) lesions of the oesophageal mucosa and of the upper airways (for points 2,3,4 evaluations by clinical examination, blood tests and instrumental tests requested by the attending physician).

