#### Determination of sample size

2.5.1

Under the hypothesis that with standard method only 42 % of catheter positioning of the NGT allow the measurement of the pH of the gastric aspirate, we want to demonstrate, with a power of 80 % and a type I error of 5 % that the 3 studied NGT allow measurement of pH in at least 62 % of positioning. Therefore, the study need 47 patients in each arm. These numbers were gathered from the current data available at IRCCS Humanitas Research Hospital. This sample size also allows us to see a difference in discomfort between the three study groups as the difference in NGT calibre could be tolerated differently (NRS scale). Following this analysis, a total of 150 patients, subdivided into 50 patients per branch, have to be included in the study.

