#### Statistical analysis

2.5.3

Continuous variables following a symmetric distribution will be presented with mean (SD), while skewed variables will be presented with median (IQR). Ordinal variables will be presented with median (IQR) and categorical variables will be presented as n (%). For primary endpoint, the percentage of catheter positioning allowing pH measurement will also be described with 95 % confidence interval. Differences among the three groups will be explored with chi square test for categorical variables, or one-way ANOVA or Kruskal Wallis test, for continuous variable, depending on their distribution shape. MP patients will also be analysed in order to explore the existence of a different pH threshold to identify the correct catheter positioning in case of use of antiacids-PPIs drugs. All analysis will be performed with Stata version 17 or superior. Statistical significance was set to p < 0.05.

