## Implications and Perspectives

3

According to international guidelines, the correct positioning of a NGT may be checked by testing the pH of aspirate, or by X-ray. The pH test method is preferrable due to lower costs as well as absence of radiation exposure for the patient. Unfortunately, pH testing is not always feasible, often due to difficulties in aspiration of current NGTs. By using new generation NGTs, designed for better aspiration but with the same, or even smaller, calibre as classical NGTs, it may become possible to more frequently avoid X-ray confirmation of NGTs insertion, without adding any additional burdens on the patients. The use of an electronic pH meter allows for more accurate measurements, which should translate to greater certainty in positioning as well as avoiding dubious results that may otherwise be an indication for X-ray. By checking correct positioning by X-ray we will further assess the sensitivity and specificity of pH testing for NGTs placement. Differentiation between the three possible latest-generation NGTs will not only look at aspiration potential, but also patient tolerability and adverse events, in order to avoid recommending NGTs that may turn out to be impractical in everyday clinical use. In particular, smaller calibre NGTs may allow for less patient discomfort, and subsequently greater compliance, ease of treatment and fewer nutrition-related adverse events. The main limitation of the study may be encountered with patients under antacid or PPI therapy, for which correct placement may give readings above pH 5.5, which are an indication for X-ray confirmation of correct placement. Unfortunately, no clinical trials exist that provide evidence on how to mitigate such factors, so we will gather data regarding possible confounding factors.

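### The global three-group chi-square is a poor basis for comparing tube complications: it does not say which tube is worse and, if complications are uncommon, a non-significant result says little about relative safety

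*Protocol article*

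**What the plan says.** Section 1.3 (Secondary endpoint) makes complications the last of the secondary outcomes: "Lastly, to evaluate possible complications associated with the positioning of the NGT and arising during the hospitalization period". It lists four kinds: mispositioning, tracheobronchial aspiration, aspiration pneumonia, and lesions of the oesophageal mucosa and upper airways. No expected rate is given for any of them.

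Section 3 (Implications and Perspectives) gives these data a purpose. Besides aspiration performance, differentiation between the tubes is to look at "patient tolerability and adverse events, in order to avoid recommending NGTs that may turn out to be impractical in everyday clinical use".

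Section 2.5.3 (Statistical analysis) has categorical variables summarised as counts and percentages, and then: "Differences among the three groups will be explored with chi square test for categorical variables". Significance is set at p < 0.05. An interval estimate is named in one place: "For primary endpoint, the percentage of catheter positioning allowing pH measurement will also be described with 95 % confidence interval".

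Section 2.5.1 (Determination of sample size) sizes the arms on pH measurability. The premise is that "with standard method only 42 % of catheter positioning of the NGT allow the measurement of the pH of the gastric aspirate", and the aim is to show that "the 3 studied NGT allow measurement of pH in at least 62 % of positioning". From this, "the study need 47 patients in each arm", raised to 50 per arm and 150 in total. The section adds that a difference in discomfort could be seen. It makes no claim about complications.

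**The concern.** The method does not fit the use. Section 3 wants to know how the tubes compare with one another on harm. A global test on three groups answers only whether some difference exists somewhere. It does not identify the tube, and a p-value gives no estimate of how large an excess remains possible.

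The arms were sized for a different, common outcome. If complications are uncommon, a non-significant result is the likely outcome even when one tube carries a several-fold excess. A reader of the results could then take the tubes to be equally safe when the data are also compatible with a material difference in, for example, aspiration or mispositioning. The choice of tube could rest partly on that.

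**Working it through.** **Inputs from the article.** 50 patients per arm in three arms; chi-square test among three groups; significance at p < 0.05; 42% and 62% for the sample size, "with a power of 80 % and a type I error of 5" per cent.

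**Assumed input.** Complication rates are not given, so two tubes are set at a rate r and the third at 3r, with r from 1% to 15%.

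**Step 1: the stated sample size.** One-sample test of a proportion against a fixed 42%, two-sided 5%:

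n = [1.960·√(0.42·0.58) + 0.8416·√(0.62·0.38)]² / (0.62 − 0.42)² = (0.967 + 0.409)² / 0.04 = 47.3.

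This agrees with the stated 47, apart from rounding. The size therefore comes from comparing each arm with a fixed historical rate for pH measurability. Complications play no part in it.

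**Step 2: power of the planned test for complications.** All outcomes of three independent Binomial(50, p) counts were enumerated, and Pearson's chi-square with 2 degrees of freedom was compared with 5.99. The expected count per arm is 50·(r + r + 3r)/3.

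| Rates in the three arms | Expected events per arm | Power |
|---|---|---|
| 1/1/3% | 0.8 | 8% |
| 2/2/6% | 1.7 | 16% |
| 5/5/15% | 4.2 | 43% |
| 6/6/18% | 5.0 | 51% |
| 8/8/24% | 6.7 | 66% |
| 10/10/30% | 8.3 | 78% |
| 15/15/45% | 12.5 | 95% |

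Power for a threefold rate passes 50% at r of about 5.9% and 80% at about 10.4%. A doubling is harder to find: power is 15% at 5/5/10%, 30% at 10/10/20% and 47% at 15/15/30%.

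**Step 3: size of the test when the tubes do not differ.** By the same enumeration, the actual type I error is 1.5% with all arms at 1%, 3.4% at 2%, 4.1% at 5% and 4.8% at 10%. For sparse events the test is conservative, because the chi-square approximation is poor there.

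**Step 4: arm size for 80% power against a threefold rate.** Using the noncentral chi-square with noncentrality n·Σ(pᵢ − p̄)²/[p̄(1 − p̄)], the test needs 593 per arm at r = 1%, 292 at 2%, 111 at 5% and 51 at 10%.

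**Step 5: what an interval shows.** With 0 events in 50, the exact (Clopper-Pearson) two-sided 95% upper limit is 1 − 0.025^(1/50) = 7.1%. One event gives 10.6% and two give 13.7%.

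Suppose the arms have 1, 1 and 5 events. The pooled rate is 7/150 = 4.67%, and chi-square = [2·(1 − 2.333)² + (5 − 2.333)²] / [50·0.0467·0.9533] = 10.67/2.224 = 4.80. This is below 5.99, so not significant. The Newcombe 95% interval for 5/50 against 1/50 runs from about −2 to +19 percentage points. The p-value alone would not show that a large excess remains possible.

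**The case against.** The strongest reply is that the article states nothing false here. Complications are a secondary outcome, the comparison is exploratory, and section 2.5.1 claims no power for them. Few trials of this size are powered for uncommon harms. Counts by arm will be visible whatever the p-value, and section 1.5 has every placement checked by chest X-ray, so mispositioning is well ascertained. Naming an interval for the primary endpoint does not rule out intervals elsewhere, and a full analysis plan may add them. All of this stands. The absence of further intervals from an article is not in itself an error.

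It does not answer the point about fit. The article names a test for categorical outcomes, and that test is weak for the comparison section 3 has in mind.

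Two stronger readings are tempting and are not supported:

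- A reader might infer that a tube with three times the complication rate would usually go undetected. That depends on the base rate, which the article does not give. It holds below about 6%. At 10% the test finds a threefold rate 78% of the time, and at 15% it does so 95% of the time. A composite of all complications, with the highest base rate, is where the claim is least secure.
- A reader might infer that p ≥ 0.05 clears a tube on safety. No section says so. Section 3 sets no test, threshold or clearance rule.

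**Conclusion.** The concern holds in a conditional form. Whatever the rates, the global chi-square does not show which tube is worse or by how much, although between-tube differentiation is its stated use. If a complication affects fewer than about 6% of patients on the other tubes, the test has under 50% power for a threefold rate at 50 per arm, and its nominal 5% level is not attained for very sparse events. A non-significant result would then be weak evidence on relative safety in either direction. For commoner complications the power objection fades for a threefold excess, but not for a doubling.

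The complication rates are assumptions; the arm size, the test and the significance level are the article's. This is a worthwhile improvement to a secondary analysis. It does not affect the primary endpoint.

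**What to change.** In section 2.5.3, for each of the four complications and for any complication:

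- report by randomised arm the number and rate with an exact (Clopper-Pearson) 95% confidence interval;
- report the three pairwise risk differences with 95% confidence intervals, for example by Newcombe's method;
- base the safety comparison on these estimates and not on the global chi-square p-value;
- state that a non-significant difference will not be read as equal safety.

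A non-inferiority margin is optional. It is needed only if the investigators want to claim that one tube is no worse than another, and it would then have to be set before the analysis.

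The cost is a few sentences and one small table from data already collected, with no added patients or procedures. The drawback is that the safety conclusion may read as inconclusive.

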
In the current context, the verification of the correct placement of the nasogastric tube is carried out through a rigorous multidisciplinary protocol. The procedure involves the aspiration of at least 5 ml of gastric secretion and the subsequent evaluation by pH test. In case of the procedure being unsuccessful, the placement is defined through chest X-ray. Based on the collected data, the percentage of patients in whom it was possible to successfully apply this protocol was 42% of all placements performed. This result highlights a limited success rate, largely associated with intrinsic difficulties encountered during the aspiration phase. These difficulties are frequently linked to the current use of nasogastric tubes, demonstrating significant complexity in implementing the multidisciplinary protocol. The data aligns with current scientific literature, indicating potential limitations in the application of this procedure. This could not only compromise nutritional benefits for the patient but also hinder cost optimization from an economic sustainability perspective. To date, existing scientific literature lacks clinical studies addressing the highlighted issues, both in terms of overcoming difficulties in gastric aspiration and adopting the use of electronic pH meters [[38], [39], [40], [41], [42], [43], [44]].

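### The sample size rests on comparing each tube with a fixed 42%, but the analysis section plans no such comparison, so the stated 80% power belongs to no planned test

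*Protocol article*

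**What the plan says.** Section 2.5.1 (Determination of sample size) starts from a benchmark: "Under the hypothesis that with standard method only 42 % of catheter positioning of the NGT allow the measurement of the pH of the gastric aspirate". The aim, "with a power of 80 % and a type I error of 5" %, is to show "that the 3 studied NGT allow measurement of pH in at least 62 % of positioning". It concludes that "the study need 47 patients in each arm", raised to 50 per arm and 150 in total.

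The benchmark is the hospital's own past experience. The Introduction reports that "the percentage of patients in whom it was possible to successfully apply this protocol was 42% of all placements performed", and section 2.5.1 says that its figures come from current data at the hospital. Section 2.2 assigns each of the three arms one of the studied tubes, and no arm receives the tube in current use.

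Section 2.5.3 (Statistical analysis) has one sentence specific to the primary endpoint: "the percentage of catheter positioning allowing pH measurement will also be described" with a 95% confidence interval. A separate, general sentence covers testing: "Differences among the three groups will be explored with chi square test for categorical variables", with one-way ANOVA or Kruskal-Wallis for continuous variables. The significance level is 0.05. The 42% does not appear in this section.

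**The concern.** The sample size section promises to demonstrate a gain over 42% with stated power and error. The analysis section answers a different question, whether the three new tubes differ from one another. If all three do equally well, which is the alternative the trial was sized on, the null hypothesis of that test is true.

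Two things are at stake. First, the sized claim has no decision rule, so the analyst would have to choose after seeing the data when superiority to 42% has been shown. That choice can change the conclusion. Second, a reader who sees a randomised trial with a p-value may take a gain over 42% as a randomised result. With no arm on the current tube, it can only be a historical comparison.

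**Working it through.** **Inputs.** From section 2.5.1: p0 = 0.42, p1 = 0.62, power 80%, type I error 5% (sidedness not stated), 47 computed and 50 planned per arm. From section 2.5.3: chi-square among three groups at 0.05.

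**Step 1: reproduce the 47.** One-sample proportion against a fixed rate, normal approximation, two-sided 5%:

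n = [(1.96·√(p0(1−p0)) + 0.842·√(p1(1−p1))) / (p1−p0)]²
= [(1.96·√(0.42·0.58) + 0.842·√(0.62·0.38)) / 0.20]² = 47.3.

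By the same approximation, power is 79.7% at n = 47 and 82.1% at n = 50. The variants tried do not give 47:

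| Calculation | n per arm |
|---|---|
| One-sample, two-sided | 47.3 |
| One-sample, two-sided, continuity-corrected | 52.2 |
| One-sample, one-sided | 37.2 |
| Two-sample, two-sided | 97 |
| Two-sample, one-sided | 77 |

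The 80% therefore refers to a test of each arm against a fixed 42%.

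**Step 2: what the named test does.** Three-group chi-square, 2 degrees of freedom, 50 per arm, 200,000 simulated trials:

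| True rates | Rejection probability |
|---|---|
| 62 / 62 / 62% | 5.3% |
| 42 / 42 / 42% | 5.2% |
| 42 / 62 / 62% | 54% |
| 42 / 42 / 62% | 53% |
| 62 / 62 / 82% | 62% |

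It cannot tell all tubes at target from all tubes at the benchmark. For one tube differing by 20 points its power is also below 80%, although section 2.5.1 claims no power for that comparison on this endpoint.

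**Step 3: what the planned interval could do.** Suppose the 95% interval is calculated per arm and success means a lower limit above 42%. At n = 50, by exact binomial probabilities:

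| Interval | Successes needed | Upper-tail error at 42% | Power at 62% |
|---|---|---|---|
| Wilson (Wald gives the same rule) | 28/50 | 3.2% | 84.6% |
| Clopper-Pearson | 29/50 | 1.6% | 76.8% |

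The method decides the borderline case. With 28/50 the lower limit is 42.3% (Wilson) or 42.2% (Wald), which passes, and 41.3% (Clopper-Pearson), which fails.

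**Step 4: one tube or all three.** Section 2.5.1 speaks of the three tubes together. With independent arms all at 62%, the chance that all three pass is 0.846³ ≈ 61% (Wilson) or 0.768³ ≈ 45% (Clopper-Pearson).

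**The case against.** The best defence is that section 2.5.3 already contains the right quantity. The confidence interval stands in the sentence specific to the primary endpoint, while the chi-square stands in a general sentence and is only exploratory. Read per arm against 42%, the interval is nearly the sized test, with 77% to 85% power at 50 per arm. This stands, and it is why the repair is small. It does not remove the gap: the text does not make the interval per arm, name a method or mention 42%, and Step 3 shows that the method can reverse the conclusion.

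A fuller protocol or an analysis plan may hold the rule. That is possible, but the point concerns two statements in this article that do not fit together, rather than detail left out.

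Some stronger readings are tempting and are not supported:

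- A reader might infer that full success would give a non-significant primary result 95% of the time. The article never calls the chi-square the primary test. A non-significant result would correctly answer whether the tubes differ.
- A reader might infer that the trial is undersized because a two-sample comparison needs 97 per arm. No such comparison is proposed.
- A reader might say that the chi-square is the only test in the plan. ANOVA and Kruskal-Wallis are also named, but for continuous variables and again between tubes.
- A reader might call the lack of a current-tube arm an error of analysis. It is a design choice, the source of the 42% is disclosed, and section 3 gives differentiation between tubes as a purpose. Randomisation serves that purpose.

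**Conclusion.** The point holds as a mismatch between sections 2.5.1 and 2.5.3. The 47 per arm comes from a one-sample, two-sided comparison with a fixed 42%, and the analysis section plans no such comparison. The only test named for this binary endpoint rejects about 5% of the time whether all tubes are at 62% or all at 42%. The stated 80% power therefore belongs to no planned test.

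This does not mean that the trial cannot address its aim. The data and the numbers per arm suffice for a per-arm rule with 76.8% to 84.6% power, depending on the interval. That range assumes a true rate of 62%, 50 analysed per arm and 42% taken as known without error. The joint figures also assume independent arms.

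**What to change.** Amend sections 2.5.1 and 2.5.3 as follows.

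1. Make the primary analysis a one-sample comparison of each arm with 42% in all randomised patients. Success is a lower limit of a named two-sided 95% confidence interval above 42%.
2. Name the interval and state its power at 50 per arm. Wilson needs at least 28/50 and has 84.6% power with an exact upper-tail error of 3.2%. Clopper-Pearson needs at least 29/50 and has 76.8% power, so the 80% would have to be restated.
3. State whether success is claimed tube by tube or requires all three. If all three, give the joint power (about 61% with Wilson, 45% with Clopper-Pearson, all tubes at 62%).
4. Label the three-group chi-square secondary and not powered, and report pairwise differences with 95% confidence intervals.
5. State that the claim against 42% is a historical, non-randomised comparison and that randomisation supports only tube-against-tube conclusions.

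The cost is wording, with no new patients or data. The downside is that the headline claim becomes openly historical and the stated power may be slightly less favourable.

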## Implications and Perspectives

3

According to international guidelines, the correct positioning of a NGT may be checked by testing the pH of aspirate, or by X-ray. The pH test method is preferrable due to lower costs as well as absence of radiation exposure for the patient. Unfortunately, pH testing is not always feasible, often due to difficulties in aspiration of current NGTs. By using new generation NGTs, designed for better aspiration but with the same, or even smaller, calibre as classical NGTs, it may become possible to more frequently avoid X-ray confirmation of NGTs insertion, without adding any additional burdens on the patients. The use of an electronic pH meter allows for more accurate measurements, which should translate to greater certainty in positioning as well as avoiding dubious results that may otherwise be an indication for X-ray. By checking correct positioning by X-ray we will further assess the sensitivity and specificity of pH testing for NGTs placement. Differentiation between the three possible latest-generation NGTs will not only look at aspiration potential, but also patient tolerability and adverse events, in order to avoid recommending NGTs that may turn out to be impractical in everyday clinical use. In particular, smaller calibre NGTs may allow for less patient discomfort, and subsequently greater compliance, ease of treatment and fewer nutrition-related adverse events. The main limitation of the study may be encountered with patients under antacid or PPI therapy, for which correct placement may give readings above pH 5.5, which are an indication for X-ray confirmation of correct placement. Unfortunately, no clinical trials exist that provide evidence on how to mitigate such factors, so we will gather data regarding possible confounding factors.

This study may not only improve the precision of NGTs placement, but could also have implications for the standardization of NGTs insertion protocols in medical institutions. It is worth noting that the knowledge gained from this study could affect and improve guidelines for NGTs placement in specific patient populations, particularly those receiving antacid or PPI therapy, where current practices are ambiguous. Furthermore, one key aspect of the study is its focus on measuring the time taken to start nutritional therapy after an NGTs placement request by a physician. This metric, quantified in minutes, is crucial in hospital nutritional care where timely delivery of nutrition can significantly impact patient recovery and quality of life. However, it has to be taken in consideration that the study's impact might be constrained by its focus on short-term outcomes, leaving an opportunity for future research to explore long-term implications and cost-effectiveness in diverse healthcare settings. Beyond the immediate clinical applications, this study's methodologies and findings could also have educational implications for clinical training and practice. By introducing new protocols for NGTs placement based on pH monitoring, there is an opportunity to revise and update training curricula for healthcare professionals, including nurses and physicians. This could lead to enhanced skill sets in NGTs management, educating a new generation of practitioners adept in utilizing advanced technologies for patient care.

